### Treatment scheme

All recruited patients fulfilling inclusion criteria and under therapy with PPI will be randomized to receive sham endoscopy, DJBL or IB implantation. Sham endoscopy and IB will be performed under sedation whereas DJBL has to be implanted under general anesthesia. To maintain blinding, all participants will receive anesthetic informed consent and anesthesia will be performed after intravenous sedation prior to intubation. The sham group will always receive conscious sedation but will not be told that the choice of anesthetic is related to the study arm. The implantation of both devices or the initial sham endoscopy and the explantation after 12 months (DJBL) will be carried out as inpatient procedures. The following endoscopies after 6 months are planned to be outpatient examinations.

All patients will receive regular dietary consultations, clinical examinations, anthropometry, taking of blood samples for analysis of comorbidities (e.g. fasting blood glucose, HbA1c, lipids, inflammatory markers) and bioelectric impedance measurement (BIA). To evaluate hepatic abscesses as might occur as a complication of DJBL, periodic abdominal sonography (US) will be conducted. Furthermore, study patients will be evaluated for concomitant medication, obesity related comorbidities and adverse events or side effects. In addition, participants will complete the SF36 quality of life questionnaire at frequent intervals (see Fig. 1 for detailed trial flow chart). To conduct the above mentioned examinations, all patients are requested to attend study visits 1, 3, 6, 12 and 24 months after implantation of the devices or initial sham endoscopy. The study participation will be completed 24 months after implantation or baseline endoscopy. In the event of premature explantation of the device (e.g. due to abdominal pain or other complications), patients will be observed for an additional 12 months. To ensure blinding of the study, only the unblinded study team is permitted to perform the explantation.

Furthermore, the success of patient and assessor blinding will be analyzed and presented.

### Safety considerations

The safety of this trial will be evaluated based on the frequency of adverse events (AEs) and serious adverse events (SAEs) defined in DIN EN ISO 14155:11, section “Discussion”.2 and section “Discussion”.37. In addition, adverse device events (ADEs), serious adverse device effects (SADEs) and unanticipated serious adverse device events (USADEs) will be determined according to Medical Devices Safety Regulation §2. All AEs will be summarized and presented for the whole study group and each individual patient. The most common AEs (occurring in at least 10% of the appropriate group) will be determined. Laboratory data will be summarized by presenting summary and changes from baseline values (means, medians, standard deviations, ranges). The analysis of safety and tolerability will be based on all patients entered either into the DJBL or IB arm who received implantation of a device.

So far, a recent overview and meta-analysis showed overall safety and SAEs to be less than 5% in both devices [11]. Minor complications were not yet reported due to inconsistency of existing studies [14]. The sham group will receive conscious sedation, for which the risk of complication is known to be very low. The possible risks associated with sedation are further reduced by the use of only small doses of sedatives that are required to ensure blinding in the sham group.

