Regarding loss of follow up, compliance in the traditional sense is not an issue in this trial. The endoscopic devices cannot be explanted by the patient and any deviations from the recommended diet are part of the “real world” behavior that should be taken into account in the trial. On the other hand, problems with implantation and device failure take the place of compliance and are expected to be an issue. The failure estimates in the available literature vary wildly in the case of the DJBL from 0/16 (0%) over the course of one year [25] to 12/25 (48%) over the course of 12 weeks [20] and it was necessary to base our estimates of 15% for the DJBL and 10% for the IB on experience from our own university hospital. Loss to follow-up after removal is difficult to estimate because of the lack of data for long-term follow-up in comparable populations, yet we estimate a conservative 10%.

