## Conclusions

Assuming they are superior to a sham procedure, the more effective and safer device between DJBL and IB could become a more standard intervention for the therapy of obesity and its complications.

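### The named safety analysis set leaves out the sham arm and any failed implantation attempt, and conflicts with the sentence promising all AEs for the entire trial population

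*Protocol article*

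**What the plan says.** Two sentences in the same paragraph of Safety considerations name different populations.

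- AE presentation: "All AEs will be summarized and presented for the whole study group and each individual patient".
- Analysis of safety and tolerability: "based on all patients entered either into the DJBL or IB arm who received implantation of a device".

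The first does not say that AEs will be shown by arm. The second names only the two device arms and makes inclusion depend on a device having been implanted.

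Other parts of the article bear on this:

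- Sample size considerations foresees unsuccessful procedures: "problems with implantation and device failure take the place of compliance and are expected to be an issue". On the rates used, it says "it was necessary to base our estimates of 15% for the DJBL and 10% for the IB on experience from our own university hospital".
- Treatment scheme collects AEs without restriction by arm: "study patients will be evaluated for concomitant medication, obesity related comorbidities and adverse events or side effects".
- Study design and setting gives sham patients a gastroscopy under sedation at the start and sedation alone at 6 and 12 months. Safety considerations comments: "The sham group will receive conscious sedation, for which the risk of complication is known to be very low".
- Study objectives lists complications and safety among the matters to be examined. Conclusions looks ahead to the outcome in which "the more effective and safer device between DJBL and IB could become a more standard intervention".

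**The concern.** A safety set should normally follow exposure to the study procedures. Here it follows the result of one of them. Whether a device ends up in place is known only after randomisation, and a complication during the attempt may itself decide it. A patient who has the anaesthesia and endoscopy but leaves without a device has been exposed to procedural risk, yet falls outside the named set. If such patients are more frequent in one device arm, the two arms are being compared on differently selected subsets.

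The second issue is the control arm. Sham patients share the sedation, the initial endoscopy, the PPI therapy and the dietary consultation, and they are followed by blinded investigators. Their AE rate is the randomised estimate of background events. Without it, the excess of, for example, gastrointestinal complaints attributable to a device cannot be separated from background within the named analysis.

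At stake are the estimates behind a stated aim of the trial and behind any later statement about which device is safer.

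**Working it through.** **The plan's own figures.** The article gives no number for the safety set, so there is none to reproduce. Its power figures serve only to confirm the arm sizes. With 60/60/30 patients and success rates of 40%, 16% and 9%:

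- the global test has 93.1% power (stated 93%);
- DJBL versus IB has 84.2% (stated 84%);
- DJBL versus sham, counted only when the global test is significant, has 89.7% by simulation (stated 88%).

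These agree within 2 percentage points. Nothing below changes them.

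**Inputs.** Total 150 (Abstract); allocation 2:2:1 (Study design and setting); failure rates 15% DJBL and 10% IB (Sample size considerations).

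**Step 1: arm sizes.** DJBL 150 × 2/5 = 60; IB 150 × 2/5 = 60; sham 150 × 1/5 = 30.

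**Step 2: certain exclusion.** Sham: 30/150 = 20%. The named set holds at most 60 + 60 = 120.

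**Step 3: possible further exclusion.** The failure rates cover implantation problems and later device failure together. A patient whose device fails after implantation stays in the set.

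- Lower end (no failure is a failed implantation): 0 patients.
- Upper end (every failure is a failed implantation): DJBL 0.15 × 60 = 9 and IB 0.10 × 60 = 6, together 15, or 15/120 = 12.5% of device-arm patients. The set would then hold 51 + 54 = 105, leaving out 45/150 = 30% of the trial.

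**Step 4: can the estimate be distorted, and which way?** Let r be the event rate in implanted patients, q the rate in failed attempts and f the share of failed attempts. The rate among all attempted is (1 − f)r + fq, so it differs from the implanted-only rate by f(q − r). The documents give no value for q. As an assumption, take r = 5%; the article cites serious events below 5% for both devices. The implanted-only analysis then shows 5% in every cell below.

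| f | q = 0% | q = 5% | q = 10% | q = 20% | q = 30% |
|---|---|---|---|---|---|
| 5% | 4.75% | 5.00% | 5.25% | 5.75% | 6.25% |
| 10% | 4.50% | 5.00% | 5.50% | 6.50% | 7.50% |
| 15% | 4.25% | 5.00% | 5.75% | 7.25% | 8.75% |

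The named set understates the all-attempted rate when q exceeds r, overstates it when q is below r, and is neutral when they are equal.

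**Step 5: the device contrast.** Keep r = 5% in both arms and use the upper-end shares (15% DJBL, 10% IB). At q = 20% the all-attempted difference, DJBL minus IB, is 7.25 − 6.50 = 0.75 percentage points. At q = 0% it is 4.25 − 4.50 = −0.25. The implanted-only analysis shows 0 in both cases. The sign depends on q, which is unknown.

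**The case against.** The best defence is that little would actually be lost. AEs are collected in all arms, the same paragraph promises to present all of them for the entire trial population and for each patient, and an independent board monitors the safety data. Sham events and failed-attempt events would therefore at least be listed. This stands, and it rules out two stronger readings that a reader might infer:

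- *That a serious event in a failed attempt would vanish from the report*, for example one perforation shown as 0 of 51 rather than 1 of 60. The promised overall and individual presentation would include it. The figure of 51 also needs every expected DJBL failure to be a failed implantation.
- *That the safety analysis has no comparator.* DJBL and IB can still be compared with each other. What the named set lacks is the sham comparator.

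A third tempting reading is *that the rule understates device risk*. That requires a higher event rate in failed attempts than in implanted patients, which is plausible for procedural harm but is given nowhere in the article. The table above shows that the effect can reverse. Some serious DJBL events listed in the Background, such as migration (4.9%) and sleeve obstruction (3.4%), can occur only with a device in place. For those, adding never-implanted patients to the denominator would dilute the rate.

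It is also fair to say that the article does not define how a partial or aborted implantation is classed, that no safety hypothesis is tested, and that the remark about the safer device is an outlook and not a decision rule.

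None of this reconciles the two sentences. A listing across the trial population is not a comparison by arm, and the sentence that names the analysis set is the restrictive one.

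**Conclusion.** The point holds as a badly fixed analysis set and an internal conflict. It is a rule the article states, not detail left to the SAP.

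- The exclusion of sham (30 of 150, 20%) follows directly from the wording and the allocation ratio.
- The exclusion of failed attempts follows from reading the condition literally. Its size is 0 to 15 device-arm patients.
- The named analysis therefore offers no randomised sham comparison of AE rates. It can distort procedural-risk estimates and the DJBL–IB comparison if failed attempts and implanted patients differ in event rate.
- Neither the direction nor the size of that distortion can be determined from the documents. The rates in the table rest on an assumed 5% and a range of assumed values for failed attempts; they are illustrations, not predictions.

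The primary endpoint, sample size and power are untouched. The change should be made before unblinding.

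**What to change.** Reconcile the two sentences in Safety considerations, and carry the result into the analysis plan:

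1. Define the safety set as all randomised patients, in all three arms, in whom a study sedation, anaesthesia or endoscopy was started.
2. Present AEs by arm and procedure attempted, with sham as the comparator, alongside the overall and individual listings already promised.
3. Keep patients with an implanted device as an additional, labelled subset, used as the denominator for events that require a device in place.
4. Report the number of attempted but unsuccessful implantations per arm, so that the difference between the two denominators is visible.

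The cost is a sentence or two of text and some additional table columns. AEs are already evaluated in all study patients, so no new data are needed, and sample size and power do not change.

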## Discussion

Obesity is a global problem leading to associated cardiovascular and endocrinologic complications and reduced quality of life [33]. Conservative programs are often ineffective [4] whereas surgical procedures are irreversible and accompanied with serious complications as well as side effects and resources are unavailable for treating most patients [6]. Thus, endoscopic procedures present an important alternative. Previous studies showed both the feasibility and safety of DJBL and IB but revealed highly inconsistent data regarding effectiveness in weight loss. Only a few trials compared endoscopic interventions with sham procedures. Although some studies reported negligible weight loss in sham groups of 2–3 kg after 12 weeks [17, 20], others found a weight loss of as high as 12 kg as high as in the IB group [15]. These considerations lead to the necessity of a prospective, multi-center, randomized, controlled trial comparing weight loss in DJBL as compared to IB and sham group.

Thus, the WET trial aims to evaluate the superiority of DJBL and IB to sham group or each other in a patient and assessor-blinded setting. The primary objective of this study is weight loss ≥10% from baseline weight one year after removal of the devices. Secondary aims comprise proportion of weight loss, changes in obesity-related comorbidities and quality of life. Furthermore, complication rates of the devices and safety will be examined due to the fact that some studies showed an elevated risk of liver abscesses after implantation of DJBL [11].

The statistic calculation was carefully performed to ensure that the study is not underpowered. The novelty of our study design is that the WET study compares two endoscopic devices with different modes of action and different implantation periods related to the sham group. To ensure blinding of the study, all patients will undergo three endoscopies or sedation without gastroscopy, respectively. Although these requirements lead to a complex study protocol, the WET study will hopefully clarify important questions in endoscopic and conservative management of obesity.

## Conclusions

Assuming they are superior to a sham procedure, the more effective and safer device between DJBL and IB could become a more standard intervention for the therapy of obesity and its complications.

## Abbreviations

DJBL: duodenal-jejunal bypass liner
EWL: excess weight loss
IB: intragastric balloon
PPI: proton pump inhibitor
US: abdominal sonography
